#### Primary outcome

The primary outcome is the patient’s score on the COMI 12 months after surgery. The COMI is a self-administered multidimensional instrument that consists of seven items which assess the extent of the patient’s back pain and leg pain, difficulties with functioning in everyday life, symptom-specific well-being, general quality of life, and social and work disability. Leg pain and back pain are assessed on 0–10 graphic rating scales and all other items on 5-point adjective scales. In each case, a higher score indicates worse status [28]. The instrument is validated in Italian and Dutch [29, 30].

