### Power considerations and statistical analysis

The primary outcome is the difference in the COMI between the study groups, 12 months after surgery. A difference of two points is considered clinically meaningful [44]. With an assumed SD of 2.5, the effect size of this difference, quantified as Cohen’s *d* is 0.80. Inclusion of 42 patients per intervention group will yield a power of 0.95 at a type-I error rate of 0.05. In addition, 42 patients with low pain catastrophizing scores will undergo the same assessments, but not receive any intervention besides care as usual. Taking into account a drop-out rate of 15%, 150 patients will be included in total.

Baseline patient characteristics will be stratified by group and presented as mean and standard deviation (SD), median and first and third quartile, and count and percentage, as appropriate. Differences in baseline characteristics between randomized groups will not be statistically tested, whereas differences with the separate control cohort will be tested using the independent-samples t-test for continuous variables, and Pearson’s chi-square test for categorical variables. In case of expected cell counts of less than 5, Fisher’s Exact test will be used instead.

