All patients randomized (i.e. those with a PCS score > 24) will be analyzed in an intention-to-treat analysis. To test for a difference between the CBT and control group in the COMI at 12 months, linear regression will be used, with correction for baseline COMI and center. In addition, the difference in the trajectory of COMI over time will be assessed by means of linear mixed-effects regression, taking all follow-up measurements into account. Adjustment for center, type of surgery, age and gender will be made and, if necessary, for other prognostic variables significantly associated with the outcome (i.e., acute postoperative pain intensity, severity of catastrophizing, preoperative depression, preoperative surgical fear, length of current sick leave, pain duration). Stepwise backward elimination using the Wald test will be used to select prognostic variables significantly associated with the outcome. Any control variables that are incomplete will be imputed if the proportion of incomplete patients exceeds 0.05. We will use multiple imputation with fully conditional specification with the number of imputations set to the percentage of incomplete patients. Predictive mean matching will be used to draw values to be imputed. Secondary outcome variables will be analyzed similar to the primary outcome. For these, logistic regression analysis adjusted for center will be used to test for differences in proportions at 12 months postoperatively.

Exploratory, we will compare the outcomes of the patients in the two intervention groups with the outcomes of patients with low pain catastrophizing scores (i.e. those with a PCS score < 24) undergoing care as usual. Linear mixed-effects regression for the three groups will be performed with primary and secondary outcomes at the three postoperative assessment periods and controlling for preoperative values. This analysis will indicate whether high catastrophizing patients follow a similar trajectory of pain and functioning after spinal fusion surgery compared non-catastrophizing patients.

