There are some limitations of our study protocol that should be mentioned. The main limitation is patient’s compliance to the intervention. In fact, very few data exist that analyze the impact and feasibility of CBT in the perioperative period after spinal fusion surgery. Another possible limitation is related to potential differences in levels of catastrophizing between the populations of the two centers. Moreover, the exact proportion of high catastrophizing patients (defined in this study as having a PCS ≥ 24) is not known in advance and could vary between the two centers. Additionally, a potential weakness of our study protocol is related to the control condition, conceived to reduce patient’s expectation bias, augmenting contact time and attention, and therefore reducing non-specific effects on outcome. It is well known in psychological research that expectation is one of the most important non-specific factors that may modulate patients outcomes [61]. However, it is difficult to know if this intervention will control for other non-specific factors that could be present (e.g. patient motivation or the therapeutic relationship between the psychologist and patients during CBT). Additionally, because of the difference in length of sessions between the CBT sessions and the education program (the latter being of a shorter duration) the factor of ‘contact time’ is not perfectly controlled for. On the other hand, the first educational session and post-discharge educational session will be held ‘face to face’ whereas all CBT sessions will be delivered by video teleconference. This ‘in-person attention’ in the two educational sessions might compensate for the shorter contact time in the control group in comparison to the CBT group.

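### The analysis is called intention-to-treat, but the primary regression uses only patients with a 12-month COMI and the imputation rule covers control variables only

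*Protocol article*

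**What the plan says.** All references are to the protocol article.

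- **Endpoint** (Primary outcome): "The primary outcome is the patient’s score on the COMI 12 months after surgery". Under Outcome measures and in Table 2, the COMI is also collected at enrolment and at 2 and 6 months.
- **Analysis set** (Power considerations and statistical analysis): all randomized patients, by intention to treat.
- **Primary test** (same section): for the 12-month difference, "linear regression will be used, with correction for baseline COMI and center".
- **Missing data** (same section): "Any control variables that are incomplete will be imputed if the proportion of incomplete patients exceeds 0.05". The article goes on to fix the method (fully conditional specification, predictive mean matching) and how many imputations to draw. It gives no rule for a missing COMI outcome.
- **Mixed model** (same section): a linear mixed-effects model on all follow-up COMI values is planned as an addition, to compare trajectories. The adjustment sentence after it names center, type of surgery, age, gender and prognostic variables chosen by backward elimination.
- **Drop-out** (same section): "Taking into account a drop-out rate of 15%, 150 patients will be included in total".

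**The concern.** A regression on one time point, with no imputation of the outcome, can use only patients who have that outcome. The promise to analyze everyone randomized and the method chosen for the primary test therefore do not match. The article does settle missing data in some detail, but for the covariates, which are the smaller problem. The 12-month outcome is where it plans for loss.

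What is at stake is the validity of the main comparison. If patients who recover poorly by 6 months are less likely to return at 12 months, and this loss is heavier in one arm, the remaining patients no longer give a fair comparison. The 6-month COMI that would correct for this will have been collected for many of them, but the primary test does not use it.

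**Working it through.** **1. The plan's own sample size.** Inputs from the power section are a target difference of 2 COMI points and an SD taken as 2.5. The figure to reproduce is this: "Inclusion of 42 patients per intervention group will yield a power of 0.95 at a type-I error rate of 0.05".

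- d = 2 / 2.5 = 0.80. A two-sided two-sample t-test at 0.05 with power 0.95 needs 41.6, so 42 per arm. Power at 42 is 0.952.
- 42 / 0.85 = 49.4, so 50 per group; 3 × 50 = 150.

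Both figures reproduce. The inflation protects 42 evaluable patients per arm, so the sample size itself treats drop-outs as lost to the analysis.

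**2. Who enters the primary regression.** Two randomized arms of 50 make 100 patients. At 15% drop-out, 100 × 0.15 = 15 have no 12-month COMI and 50 × 0.85 = 42.5 per arm remain. Power is 0.954 with 42.5 per arm and would be 0.977 with 50 per arm. The loss is already paid for.

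**3. Size of a possible bias.** The article gives no drop-out by arm and no link between drop-out and recovery, so these are assumptions:

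- 50 per arm, SD 2.5, true effect 0
- correlation of follow-up COMI with baseline 0.5
- 6-to-12-month correlation given baseline 0.75
- log-odds of a missing 12-month value rising by 1 per SD of worse 6-month COMI

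The completers' 12-month COMI is regressed on arm and baseline COMI. With bias b and standard error SE, type I error = 1 − Φ(1.96 − |b|/SE) + Φ(−1.96 − |b|/SE). The simulated SE is about 0.467.

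| Missing, CBT vs control | Bias (negative favors CBT) | Type I error |
|---|---|---|
| 15% vs 15% | 0.00 | 0.050 |
| 18% vs 12% | −0.07 | 0.053 |
| 22% vs 11% | −0.13 | 0.059 |
| 26% vs 7% | −0.22 | 0.077 |
| 22% vs 11%, log-odds 0.5 per SD | −0.07 to −0.08 | 0.053 |

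Example, second row: 0.07 / 0.467 = 0.150, so 1 − Φ(1.810) + Φ(−2.110) = 0.035 + 0.017, or 0.053 before rounding of the terms. In the fourth row, repeated runs gave biases from −0.20 to −0.23 and type I errors from about 0.07 to 0.077.

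Against the 2-point target, 0.07 / 2 = 3.5% and 0.22 / 2 = 11%.

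**4. Does using the earlier COMI help?** In the same simulations, predicting the missing 12-month values by arm from baseline and 6-month COMI brings the bias to about 0 in every 1-per-SD scenario. With equal drop-out the gain is only precision: SE 0.454 instead of 0.467, about 3%.

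**The case against.** **The exclusion is inferred.** The article never says that patients without a 12-month COMI are dropped, and outcome-missingness rules are often left to a full protocol or analysis plan. This is fair as far as it goes. But the article states an imputation rule, details it and limits its scope, alongside a promise to analyze everyone. The point is the scope of a stated rule, not an absent detail.

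**The mixed model already uses the earlier visits.** True, and it keeps patients who miss month 12 but have an earlier follow-up. It is additional, however, targets the trajectory and is described with different covariates. It can expose a discrepancy but does not decide the primary test.

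**The bias depends on assumptions.** This stands. It needs drop-out that is both related to outcome and different between arms, and the documents establish neither.

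Several stronger readings are tempting, and the documents do not support them:

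- *That compliance problems show differential drop-out.* The Discussion says "The main limitation is patient’s compliance to the intervention", but that concerns attending and following the intervention, not missing questionnaires. Scheduled CBT contact is longer (90 + 5 × 60 = 390 minutes, against about 120 to 140 for control). Controls, however, also have six contacts, two of them in person, plus exercises and an 8-week diary. Which arm would lose more patients is unknown.
- *That the bias could reach 0.4 points.* That needs 25% vs 5% missing and drop-outs 2 points worse than completers (0.25 × 2 − 0.05 × 2 = 0.4). If earlier COMI explains the gap, this is the mechanism in step 3 at a more extreme setting. If not, neither a mixed model nor standard imputation would remove it.
- *That the 5% threshold for covariates also depletes the primary test.* That model contains only baseline COMI and center. Center is the randomization stratum and COMI is collected at enrolment, so the effect is negligible.
- *That patients whose surgery is cancelled have no endpoint.* The article does not discuss such patients, so this is speculation.
- *That the trial is underpowered.* Step 2 shows that it is not.

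**Conclusion.** The point holds as a mismatch between the stated analysis population and the stated primary method. About 85 of 100 randomized patients would be expected in the primary test. This assumes that the 15% drop-out means no 12-month COMI, which is the natural reading because the inflation restores 42 evaluable patients per arm.

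The likely harm is modest: no bias under equal drop-out, and about 0.07 to 0.22 points with type I error of 0.053 to 0.077 under the assumed unequal, recovery-dependent drop-out. The negative sign follows from assuming heavier loss in the CBT arm; heavier loss in the control arm would reverse it. This is a should-fix. It does not invalidate the design, but it bears on the main conclusion and can be repaired with data and methods already planned.

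**What to change.** Choose one of these as the primary estimate:

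- **Mixed model.** Take the 12-month CBT-control contrast from the planned mixed model on 2-, 6- and 12-month COMI, with treatment-by-time, baseline COMI and center named as its terms. This includes every randomized patient with at least one follow-up COMI.
- **Imputation.** Keep the linear regression, but extend the planned multiple imputation to the 12-month COMI, by arm, using baseline, 2- and 6-month COMI. This can also include patients with no follow-up visit, who then rest on baseline alone.

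Either way, state which patients the primary analysis contains, and add one sensitivity analysis that shifts the unobserved 12-month values by a fixed delta, to cover data missing not at random.

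The cost is a change of wording and a little more analysis work. Sample size, visits and questionnaires stay as they are. The price in assumptions is reliance on data being missing at random given the observed COMI, which the delta-shift analysis is there to probe.

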A non-randomized group, consisting of low catastrophizing patients (score < 24 PCS), will be included as an observational cohort. These patients will not undergo any additional intervention besides usual care but will undergo the same data-collection as the high catastrophizing randomized groups.

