### Randomization

A computer-generated randomization will be used to allocate the participant to either CBT or educational program with a 1:1 allocation. We will use block randomization stratified by center, with block sizes of 6. The randomization is performed by the Principal Investigator per site, who is not blinded for group assignment. The patients will be randomized immediately after they are included and have completed the PCS (one of the baseline assessments) to be able to make two pre-operative appointments with the patients in the intervention and control group.

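### The exploratory comparison with the non-randomized low-PCS cohort names only preoperative values as controls, so it may be confounded by center and case mix

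*Protocol article*

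**What the plan says.** In the protocol article, the section on power considerations and statistical analysis gives each model its own covariates.

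- Randomized comparison of the COMI at 12 months: "linear regression will be used, with correction for baseline COMI and center".
- Randomized mixed model over all follow-up visits: "Adjustment for center, type of surgery, age and gender will be made", plus further prognostic variables chosen by backward elimination.
- Three-group model with the low-PCS cohort: "Linear mixed-effects regression for the three groups will be performed with primary and secondary outcomes at the three postoperative assessment periods and controlling for preoperative". Preoperative values are the only controls named. This stands in a separate paragraph that opens "Exploratory, we will compare the outcomes of the patients in the two intervention groups with the outcomes of patients with low pain catastrophizing scores".

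The Randomization section states "We will use block randomization stratified by center, with block sizes of 6", which covers the high-PCS patients only. For the others, Participants and recruitment says "A non-randomized group, consisting of low catastrophizing patients (score < 24 PCS), will be included as an observational cohort". It gives no center target, matching or sampling rule for them.

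Baseline characteristics will be tested between the randomized patients and this cohort, but no adjustment is tied to the result. Among the limitations, the Discussion says of the two sites that "the exact proportion of high catastrophizing patients (defined in this study as having a PCS ≥ 24) is not known in advance and could vary".

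**The concern.** The comparison that randomization already balances by center is also adjusted for center and case mix. The comparison with no design protection is given neither. PCS alone decides which group a patient enters. If the share with PCS ≥24 differs between the Swiss and the Dutch site, the high and low groups can have a different center mix.

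Center can affect outcome by routes that the preoperative score need not capture. The sites are in different countries and use different language versions of the questionnaires. The Discussion says that in many health systems the indication for fusion depends on hospital factors, preferences and reimbursement. Postoperative physical therapy may be outpatient or inpatient.

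The authors intend to use the result. The analysis section says it will show whether high catastrophizers follow a trajectory similar to that of non-catastrophizing patients. The Discussion uses it to judge whether CBT brings patients to the level expected in low catastrophizers. It adds that, if CBT is not superior and high catastrophizing is confirmed to worsen outcome, this might be a reason for reluctance to offer these patients fusion.

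**Working it through.** **The plan's own figures.** With a difference of 2, SD 2.5 and two-sided alpha 0.05, 42 per group gives a power of 0.952 by the two-sample t-test (stated: 0.95). For drop-out, 42/0.85 = 49.4, so 50 per group, and 3 × 50 = 150. Both figures reproduce. The point does not turn on them, but the group size and SD are used below.

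**Covariates side by side.**

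| Model | Protected by design | Covariates named |
|---|---|---|
| CBT v control, 12-month COMI | Randomized, center-stratified | Baseline COMI, center |
| CBT v control, mixed model | Randomized, center-stratified | Center, type of surgery, age, gender, selected prognostic variables |
| Three groups, mixed model | None for high v low | Preoperative values |

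**Size of a center bias.** Let p_H and p_L be the shares of the high and low groups that come from site 1. Let g be the difference in 12-month COMI between sites that remains after control for the preoperative score. With center left out of the model, the spurious high-versus-low difference is

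bias = (p_H − p_L) × g.

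The documents give neither the shares nor g, so all of these values are assumptions. The false-positive rate is for one randomized arm against the cohort (42 v 42, SD 2.5, true difference 0, two-sided 5%, normal approximation). The standard error is 2.5 × √(2/42) = 0.55.

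| Center split, high v low | g | Bias (COMI points) | False-positive rate |
|---|---|---|---|
| Equal | any | 0 | 5.0% |
| 60/40 v 40/60 | 0.5 | 0.10 | 5.4% |
| 60/40 v 40/60 | 1.0 | 0.20 | 6.6% |
| 60/40 v 40/60 | 1.5 | 0.30 | 8.5% |
| 70/30 v 30/70 | 0.5 | 0.20 | 6.6% |
| 70/30 v 30/70 | 1.0 | 0.40 | 11.3% |
| 70/30 v 30/70 | 1.5 | 0.60 | 19.6% |
| 80/20 v 20/80 | 0.5 | 0.30 | 8.5% |
| 80/20 v 20/80 | 1.0 | 0.60 | 19.6% |
| 80/20 v 20/80 | 1.5 | 0.90 | 37.8% |

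For the middle case, (0.70 − 0.30) × 1 = 0.4, and 0.4/2 = 20% of the clinically meaningful difference.

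**What the middle case requires.** Suppose both sites screen at the same rate and patients enter as they come. Let h1 and h2 be the shares with PCS ≥24 at the two sites. Then p_H = h1/(h1 + h2) and p_L = (1 − h1)/(2 − h1 − h2). With h1 = 0.7 and h2 = 0.3, p_H = 0.7/1.0 = 0.70 and p_L = 0.3/1.0 = 0.30. So at equal screening rates the 70/30 split needs shares of 70% and 30%, which is a large difference between sites. With 60% and 40% the split is 60/40 v 40/60.

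An additive center effect disappears when center is in the model. Control for the preoperative score removes only the part that runs through that score.

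**The case against.** The strongest reply is that this is one exploratory, unpowered analysis described in a condensed article. The text does not say that the earlier covariates are dropped, and the full analysis plan may list them. Baseline differences with the cohort will be tested, and the case-mix data are collected. The illustrated bias is also modest: 0.4 points is below one standard error, both for one arm against the cohort (0.55) and for both arms pooled (2.5 × √(1/84 + 1/42) = 0.47).

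Part of this stands. The analysis is labelled exploratory, the size is hypothetical, and the absence of other covariates is read from a list, not from an explicit exclusion. But the article does more than stay silent: it states a control set for this model, and that set is thinner than the one for the randomized mixed model. The baseline tests lead to no adjustment, and with about 42 patients in the cohort a non-significant test does not exclude a relevant imbalance.

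A reader might infer three stronger points that the documents do not support:

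- **That the authors expect catastrophizing to differ by center.** They call the differences potential, list them as a possible limitation, and say the share could vary.
- **That the comparison is confounded.** Bias needs both a center imbalance and a residual center effect. Neither is quantified, and a large site with a low share of high-PCS patients could supply many patients to both groups.
- **That cohort entry needs a quota per center.** Consent precedes the PCS, so a quota could turn away patients who have already consented. Recruitment began in February 2020, so it could not apply from the start. Adjustment alone removes an additive center effect.

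**Conclusion.** The point holds as a gap in an exploratory analysis. Followed as written, the three-group model leaves the high-versus-low comparison open to confounding by center and case mix, and the authors plan to draw a substantive conclusion from it. The primary comparison of CBT with control is randomized, stratified by center and adjusted for center, so it is unaffected.

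Under the assumed splits and center effects, the bias runs from 0 to 0.9 COMI points. The middle case is 0.4, and the bias is zero if the center mix is equal. These figures show what could happen; they do not estimate what will. They assume an additive center effect that remains after control for the preoperative score.

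**What to change.** Add one sentence to the paragraph on the three-group analysis: center, type of surgery, age and gender enter the mixed model as fixed covariates, as they do in the randomized mixed model, in addition to the preoperative value of the outcome. Report the number of patients per center in each of the three groups, so that readers can see how far the comparison rests on overlap between the sites. PCS severity should not be added, since PCS defines the groups being compared.

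All these variables are already collected. The sample size and enrolment do not change, and the sentence can be added at any time before the analysis. The cost is a few degrees of freedom. If the covariates are not added, the conclusion about similar trajectories should be worded as unadjusted for center and case mix.
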